## 3.12 Data Management Plan:

### 3.12.1 Data collection tool development plans

To ensure consistency and minimization of errors in the data collected, standardized methods of data management will be used across the trial sites. This will start with development of common data collection tools to be administered at each of the trial sites. The tools will contain the common elements to be administered at all sites, and elements that may be administered by one or two sites only. Prior to the tools being adopted, Site Leaders and their respective research team members will discuss each tool and agree on the minimum set of common questions/ data items to be collected at all the three sites. Each site may thereafter add any site-specific questions of interest.

### 3.12.2 Database development plans

Once the content of the data collection tools has been agreed upon and finalized; common data entry formats will be developed in an appropriate data management and easy to use software, e.g. REDCap or EPIDATA. The data entry formats will then be sent to the three study sites, and pilot testing of these data entry formats conducted using pilot/ pre-test data. Should a given site opt to use a different software, they will do so but the variable names and their formatting will be maintained at all sites to enable quick merging of the data at the end of the trial. Any required corrections will be made before initiation of the main trial activities. This approach will ensure that data from each site can easily be merged to perform overall intervention analysis that includes data from all the three sites.

### 3.12.3 Data management

As a standard operating procedure, completed questionnaires and other data collection tools will be checked by designated data collection supervisors at each site, for missed entries, inconsistencies and any other obvious errors on the completed tools. In case errors are identified, the responsible data collection personnel will attempt to correct, and/or contact participant where possible. Once the completed tools have been checked and cleared by the respective data collection supervisor, they will be logged with the data entry supervisor for data entry.

Except when a site opts to use electronic data capture methods, for example using tablets, all on completed questionnaires and other data collection tools will be double entered (by two different data entry personnel), to minimize data entry errors. Variance in values of the data entered will be periodically generated (at least once a week), and the errors corrected. Each site will be responsible for ensuring that data cleaning is conducted at adequate frequency.

## 3.13 Statistical analysis Plan

### 3.13.1 Primary intervention efficacy analysis:

We will use intention-to-treat analyses for all primary outcomes, that is, all participants will be analyzed as assigned to their respective study arms. Since the unit of analysis for the primary outcome of interest are the individual participants, to minimize the effect of within cluster correlations, we will employ generalized estimating equations (GEEs) to evaluate changes over time in HbA1c values as a continuous variable among participants with pre-diabetes; and the proportion of participants with stabilized plasma glucose among participants with diabetes, in relation to assigned trial arm. Thus we use multivariable linear regression mixed effects modeling with a random intercept, unstructured correlation matrix and robust standard errors, to evaluate changes over time in HbA1c, and logistic regression analysis to compare the proportion of participants with stabilized plasma glucose among participants with diabetes.

Missing data are expected due to missed appointments, drop-outs, loss-to-follow-up and/or death. One technique to deal with missing data when the outcome is continuous, is hierarchical linear modeling (HLM; also called random effects regression) [Singer et al. 2003].

We do not anticipate differences in the intercept within each site, as randomization is expected to balance out baseline differences between the groups. However, there may be differences in the intercepts between sites, reflecting differences within the client populations in each site. We anticipate that the primary factor affecting the slope (i.e., the rate of change of the outcome measure) will be group membership (i.e, facility only or facility plus community intervention). If there is any significant unexplained variance after baseline differences and site membership have been accounted for, we can look for other factors influencing the slope, such as sex, age, co-morbidities, etc. Another analytic option that will be considered is generalized estimating equations (GEE) [Zeger et al. 1986], which can adjust for clustered, serially correlated data with missing values. The choice of techniques will be based on the nature of the data.

The analysis plan will combine the study groups across sites. However, it may turn out that the demographic characteristics of participants and available treatments differ so widely from site to site that this will not be possible. In that case, it will be necessary to compare each treatment group to its site-specific study groups.

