# 3.0 DESIGN AND METHODS

## 3.1 Study Design:

A stratified cluster-randomized trial design will be used. At each of the study sites, the clusters will be the catchment areas of participating health facilities. The health facility clusters will be randomized to either the facility alone arm, or the facility + community arm. Thus each health facility to participate in the trial, together with the community in its catchment area will be the units of randomization. Although the clusters will be the units of randomization, the enrolled individual participants will be the primary study units of measurement.

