**3.6.2.** **Facility recruitment**

Recruitment will take place at the two selected facilities. Persons presenting at the facilities who are either diagnosed with T2DM, or present with NCDs risk factors, including obesity, high blood pressure and/or impaired glucose tolerance, will be invited to participate in the trial. They will be recruited when visiting the facility for routine clinical care or upon referral from the community as per the above outlined protocol. Subjects will be classified as diabetic if two consecutive FPG tests > 6.9 mmol/L and as pre-diabetic if two consecutive FPG tests are between 6.1-6.9 mmol/L. A third FPG test may be needed to validate different test results (Figure 13 and Table 13).

Following eligibility confirmation, an ‘Eligibility Confirmation Form’ will be administered and written informed consent sought from the subject prior to study enrollment. Briefly, the study manager at the health facility will provide information on SMART2D study objectives, procedures, benefits and risks of participating, as well as confidentiality issues. Participants will receive a consent form and continue to receive standard medical care as needed, and as available at the health facility. Administration of any study procedures will only happen after eligible subjects have consented to participate in the study, upon which they will be enrolled and given a unique study number.

*Figure 13 Algorithm for sequence of screening tests for South Africa*

[figure not shown]

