$\mu_{0}$ = mean value of outcome variable (HbA1c) at month 12 in the comparison (control) arm

$\left( \mu_{0}-\mu_{1} \right)$ = minimum effect size to be detected

[figure not shown]

[figure not shown]

The necessary sample size for a cluster randomized trial depends on the variation in the intervention effects between the arms, and the clustering due to trial arm allocation (which reduces the variance of the difference between the arms), and the correlation between the repeated observations in each participant. Given that we have a fixed number of health facilities (clusters), to adjust for clustering we used a formula for fixed number of clusters and fixed number of participants within clusters as described in Hemming et al (2011) page 19 [Hemming et al. 2011].

$$Sample size per cluster=\frac{n_{i}*k*\left( 1-\rho\right)}{\left( k-n_{i}*\rho\right)}$$

where: $n_{i}$ = initial sample size

$k$ = number of clusters

= inter-cluster correlation

[figure not shown]

[figure not shown]

It is important to note that each site will be using different numbers of clusters; specifically Uganda will be working in 9 clusters, Sweden in 4 clusters, whereas South Africa will be working in 2 clusters. Thus different inter-cluster correlation (ICC) coefficient values are expected. We were unable to find published literature providing estimates for ICC coefficients for HbA1c among persons with pre-diabetes. We therefore explored various values of ICC coefficients for each site, and used values that provided the highest sample sizes to detect the desired effect size. For Uganda we used an ICC value of 0.200 to obtain a sample size of 112 participants, for South Africa we used an ICC value of 0.044 to obtain a sample size of 129, whereas for Sweden we used an ICC value of 0.06 to obtain a sample size of 79; all per study arm. For Sweden, there will be a further interest to compare the primary outcome of interest between immigrant participants of non-European origin versus immigrant participants of European origin. In order to allow for this sub-analysis, the sample size of 79 for Sweden was doubled to 158 to enable detection of the same effect size between immigrant participants of non-European origin versus immigrant participants of European origin.

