### 3.13.2 Analyses of secondary objectives

1. For the "incidence of progression from pre-diabetes state to diabetes state", we will use Kaplan Meier methods to compare incidence between the two arms. The log-rank test will be used and Kaplan-Meier curves will be plotted for each treatment group.
2. Adverse events, including hospitalizations due to hypo- or hyperglycemia, morbidity. For adverse events outcomes, we must account for the possibility that participants may experience multiple episodes over the study period. Thus, we will use log-binomial models for repeated outcomes to examine the treatment effect on these outcomes
3. For costs outcomes, cost evaluation will be undertaken from the health program provider perspective. The health service use costs of the two strategies will be calculated at 12 months in both arms. Costs incurred between baseline and 12 months will be discounted at ??%. The mean cost of the two groups over 12 months will be compared using non-parametric tests. Results will be reported with 95% confidence intervals and uncertainty will be examined using sensitivity analysis. An incremental cost-effectiveness ratio will be calculated over the 12 months of the intervention. The need or otherwise for cost-effectiveness modeling will depend on there being economically important clinically significant differences in glycaemic control, as determined by the likely impact on and hence, long-term effects on morbidity and mortality. Whether any differences in glycaemic control are important will be informed by reviewing the cost-effectiveness of other interventions that have been evaluated using lifetime models. If such differences do exist, the modeling of the longer-term effects to assess the incremental cost per quality adjusted life-year will be conducted
4. For comparison of differences between the country sites, in regard to baseline context infrastructure situation for prevention and management of diabetes, these are baseline comparisons thus for continuous context variables, we will use the t-test statistic or the equivalent non-parametric test. For categorical context variables we will use the chi-square test statistic.

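### Robust-SE and GEE models without a small-sample correction are planned for 15 clusters, and the conversion and cost tests name no allowance for clustering, so error rates exceed 5%

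*Protocol*

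**What the plan says.** Section 3.1 makes the facility and its catchment the unit of randomisation: "The health facility clusters will be randomized to either the facility alone arm, or the facility + community arm". Section 3.10 gives the counts: "specifically Uganda will be working in 9 clusters, Sweden in 4 clusters, whereas South Africa will be working in 2 clusters". Section 3.2 has three arms in Uganda and two elsewhere. For South Africa, section 3.6.2 adds: "Recruitment will take place at the two selected facilities".

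For the primary outcomes, section 3.13.1 says "we will employ generalized estimating equations (GEEs) to evaluate changes over time in HbA1c values". It then describes "multivariable linear regression mixed effects modeling with a random intercept, unstructured correlation matrix and robust standard errors" for HbA1c and logistic regression for the diabetes outcome, and leaves the final choice of technique to the data. Countries are to be combined. If participants and available treatments turn out to differ too widely between sites, "it will be necessary to compare each treatment group to its site-specific study groups". Section 3.10 also sizes each country so that its arms can be compared on their own.

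For conversion from pre-diabetes to diabetes, section 3.13.2 says: "The log-rank test will be used and Kaplan-Meier curves will be plotted for each treatment group". For costs, taken from the provider perspective, it says: "The mean cost of the two groups over 12 months will be compared using non-parametric tests". Neither item mentions clusters.

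**The concern.** Sandwich standard errors are justified by a large number of independent clusters. With few clusters they are biased downwards and, used with a normal reference, reject too often. Here the largest two-arm comparison has 12 clusters and the smallest has 2. If the random intercept and the robust errors sit at participant level instead, they deal with repeated measurements and leave facility clustering unaddressed.

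At stake are the p-values and intervals for both primary glycaemic outcomes, every country-specific claim, the conversion outcome, and the provider-cost comparison (primary objective 4).

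**Working it through.** **1. Cluster counts.** The protocol's own adjustment, n = n_i·k·(1 − ρ)/(k − n_i·ρ), confirms that its sample sizes rest on 9, 4 and 2 clusters. For pre-diabetes with n_i = 34:

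- Uganda: 34·9·0.800/(9 − 6.8) = 111.3, so 112, as stated.
- South Africa: 34·2·0.956/(2 − 1.496) = 128.98, so 129, as stated.
- Sweden: 34·4·0.93/(4 − 2.38) = 78.07, so 79, as stated, using the ICC of 0.070 in Table 16(a). The ICC of 0.06 in the text gives 66.

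Assuming equal allocation, clusters per arm are 9/3 = 3, 4/2 = 2 and 2/2 = 1. Pooled, facility + community against facility only is 3 + 2 + 1 = 6 per arm.

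**2. Uncorrected robust z test.** With c equal-sized clusters per arm and no covariates, the sandwich variance of the arm difference is (c − 1)/c times the unbiased cluster-level variance. The test therefore rejects when |t| on 2c − 2 df exceeds 1.96·√((c − 1)/c).

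| Comparison | c per arm | Effective cut-off | df | Type I error | Widening needed for a 95% interval |
|---|---|---|---|---|---|
| Pooled, no country terms | 6 | 1.79 | 10 | 10.4% | 1.25× |
| Uganda, pairwise | 3 | 1.60 | 4 | 18.5% | 1.73× |
| Sweden | 2 | 1.39 | 2 | 30.0% | 3.1× |
| South Africa | 1 | not defined | 0 | no test | not estimable |

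Simulated exchangeable GEE with sandwich errors agrees: 16.9% (HbA1c) and 18.6% (binary) in Uganda, 31.5% and 31.0% in Sweden, and 10.2% pooled. Section 3.13.1 expects intercepts to differ between countries. With country terms added and equal cluster sizes, simulation of the pooled robust z test gives about 15%. A cluster-level t test on the same 12 clusters, with 12 − 3 − 1 = 8 df, holds 5%.

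**3. South Africa.** With one facility per arm, an arm-only model fits both cluster means exactly, so the facility-clustered robust SE is 0. With covariates it is close to 0. If clustering is instead handled only at participant level, the protocol's ICC of 0.044 with 129 per cluster gives a design effect of 1 + 128·0.044 = 6.63 and a type I error of 2·(1 − Φ(1.96/√6.63)) = 45%.

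**4. Tests without a cluster term.** The design effect is DE = 1 + (m − 1)·ICC and the type I error is 2·(1 − Φ(1.96/√DE)). In Uganda m = 112/3, about 37. The protocol gives no ICC for conversion or cost, so 0.01 to 0.10 is an assumption.

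| Assumed ICC | DE | Type I error |
|---|---|---|
| 0.01 | 1.36 | 9% |
| 0.05 | 2.80 | 24% |
| 0.10 | 4.60 | 36% |

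A simulated log-rank test (detection at months 3, 6 and 12; assumed 12.5% yearly conversion) gives 9% to 39% over this range. A simulated Mann-Whitney test on costs with 43 per cluster gives 10% to 41%.

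**The case against.** The strongest reply is that the protocol pools first. The severe figures belong to country-specific analyses, and a reader might wrongly infer that the main pooled result runs at 18% to 30%. It does not: pooled inflation is about two to three times nominal. But country-specific inference is a stated purpose of the sample size, and comparisons with Uganda's current-practice arm can only be 3 against 3.

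Degrees-of-freedom details are often left to a statistical analysis plan, and section 3.13.1 states no normal reference. That is fair. The figures describe the uncorrected default. Still, the section does name robust errors, and it leaves the level of the random intercept open.

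Other stronger readings also fail:

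- **The fallback is baseless because country differences do not bias a within-country comparison.** The trigger also cites differing treatments, and sections 3.3.2.3 and 3.3.3.3 show that delivery does differ. Reluctance to quote one pooled effect is defensible. What stands is that the trigger is vague and moves inference to where it is weakest.
- **Sweden is certainly 2 against 2.** Section 3.6.3 says postal-code zones were randomly allocated, without giving their number.
- **A log-rank test is empty because HbA1c is measured only at baseline and month 12.** Table 15 schedules FPG at months 3, 6 and 12 in Uganda and South Africa, although the data-collection tools limit interim FPG monitoring to Uganda. The objection holds fully only for Sweden.
- **Costs are compared by rank tests, for both cost objectives.** The text says only non-parametric, which could mean a bootstrap of means, and it covers only the provider perspective.
- **Conversion and cost tests have about 49% error.** That borrows the ICC of 0.20 chosen for HbA1c in Ugandan pre-diabetes.

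**Conclusion.** The point holds. As written, the primary inference rests on too few clusters for uncorrected robust errors. At nominal 5%, type I error is about 10% pooled, or about 15% with country terms; about 18% in Uganda; and about 30% in Sweden if four clusters are randomised. South Africa supports no valid site-specific test, because the facility effect and the arm effect cannot be separated and no correction changes that.

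For conversion and provider costs, the certain part is that no allowance for clustering is named. The size, roughly 10% to 40% in Uganda, depends on the assumed ICC range. The primary-outcome figures assume equal allocation, equal cluster sizes and a normal reference. Weighting large clusters by their size would push the pooled figure with country terms higher, to a little over 20%.

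**What to change.** - **Primary analysis:** specify a country-stratified comparison with the randomised cluster as a random effect, adjusted for baseline HbA1c. Use Kenward-Roger degrees of freedom or a cluster-level t test (12 − 3 − 1 = 8 df for facility + community against facility only). For the binary diabetes outcome the cluster-level version is the simpler choice.
- **Fallback:** keep this as the primary inference whether or not countries differ in demographics. Show country-specific results beside it, with cluster-based df for Uganda and Sweden. Report South Africa as an estimate with no site-specific p-value or claim of effect.
- **Sweden:** reconcile sections 3.1 and 3.10 with 3.6.3 on what was randomised. If it was zones, the zone is the cluster and the df must be recounted.
- **Conversion:** use a cluster-adjusted analysis, with a month-12 binary outcome where there is no interim glucose (Sweden) and a discrete-time or interval-censored model where interim FPG exists. State whether South Africa collects it.
- **Provider costs:** compare arithmetic means with a cluster-level, country-stratified method.

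This changes analysis wording only and needs no new data. The price is wider intervals: the critical value on 8 df is 2.31 instead of 1.96, and the country-specific intervals widen far more.

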|  | Study informed consent |  | X |  |  |  |
|  |  |  |  |  |  |  |
| **II. Enrollment & Study ID** | Study ID number assignment |  | X |  |  |  |
|  | Patient registration in Register |  | X |  |  |  |
|  | Patient file creation |  | X |  |  |  |
|  | Patient appointment card |  | X |  |  |  |
|  |  |  |  |  |  |  |
| **III. Physical Measurements** | Height |  | X |  |  |  |
|  | Weight |  | X | X | X | X |
|  | Waist circumference |  | X |  | X | X |
|  | Blood pressure |  | X | X | X | X |
|  | 7-day pedometer steps |  | X |  |  | X |
|  |  |  |  |  |  |  |
| **IV. Biochemical** | FPG (Uganda & South Africa) | X, X | X | X | X | X |
|  | HbA1c (All sites) |  | X |  |  | X |
|  |  |  |  |  |  |  |
| **V. Basic participant data** | Pre-eligibility assessment | X |  |  |  |  |
|  | Eligibility confirmation |  | X |  |  |  |
|  | Eligibility and recruitment check |  | X |  |  |  |
|  | Contact Information |  | X |  |  |  |
|  | Demographic and social measures |  | X |  |  |  |
|  | Medical and medication history |  | X |  |  |  |
|  | Behavioral measures (diet, physical activity, foot care, tobacco use, alcohol consumption) |  | X |  |  | X |
|  |  |  |  |  |  |  |
| **VI. Intervention process measures** | Participant diabetes knowledge |  | X |  |  | X |
|  | Illness perception |  | X |  |  | X |
|  | Social support and sources of support |  | X |  |  | X |
|  | Self-efficacy, autonomy support & self-regulation |  | X |  |  | X |
|  | Psychological adjustment |  | X |  |  | X |
|  | Quality of life & Stress |  | X |  |  | X |
|  | Diabetes treatment satisfaction |  |  |  |  | X |
|  | Out of pocket expenditure |  |  | X | X | X |
|  | Incremental cost to the health facility |  |  | X | X | X |
|  | Adherence to study procedures and to intervention elements |  | X |  |  | X |
|  |  |  |  |  |  |  |
| **VII. Facility forms** | Process evaluation |  |  | X | X | X |
|  |  |  |  |  |  |  |
| **VIII. Community forms** | Environment context measurement (EPOC) |  | X |  |  |  |

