## 3.10 Sample size Determination

Although the overall aim during data analysis will be to combine participants across all the three country sites, it is recognized that: a) there will most likely be baseline differences across the country sites reflecting the different population characteristics between the countries; and, b) each site will want to analyze data from their site-specific arms. Thus the sample was calculated such that differences between the trials arms in regard to primary outcomes can be detected at each study site separately when desired.

The sample size for this trial has been determined based on the primary hypothesis that by the end of follow-up, the “facility plus community” arm will be superior to the “facility alone” arm, and the current practice arm in Uganda, with respect to: a) mean HbA1c readings among participants with pre-diabetes, and b) the proportion of participants with diabetes with controlled blood sugar levels.

*Sample size for participants with pre-diabetes*

With the aim of being able to detect an average difference between any two trial arms, in mean HbA1c by month 12 of at least 3 mmol/mol (effect size), with a standard deviation of 2.5 mmol/mol in the intervention arm, and a standard deviation of 2.5 mmol/mol in the comparison (control) arm; the required sample size before adjusting for clustering, at an 80% power and 5% level of significance is 34 participants per arm. For this first stage calculations, we used the formula as described in Hayes and Bennett (1999) [Hayes et al. 1999] for a continuous outcome:

$$Initial sample size(n_{i})=\left[ \frac{\left( Z_{\alpha/2}+Z_{\beta} \right)^{2}*\left( \sigma_{0}^{2}+\sigma_{1}^{2} \right)}{\left( \mu_{0}-\mu_{1} \right)^{2}} \right]$$

where: $Z_{\alpha/2}$ = standard normal distribution value at $\alpha$ level of significance

= standard normal distribution value at level of significance

[figure not shown]

[figure not shown]

[figure not shown]

[figure not shown]

$\alpha$ = level of significance

= type 2 error, for which (1-$\beta$) is the power of the study to detect the desired effect size

[figure not shown]

[figure not shown]

$\sigma_{0}^{2}$ = variance of outcome variable (HbA1c) at month 12 in the comparison (control) arm

$\sigma_{1}^{2}$ = variance of outcome variable (HbA1c) at month 12 in the intervention arm

$\mu_{1}$ = mean value of outcome variable (HbA1c) at month 12 in the intervention arm

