5. Similarly, for the degree of implementation of the intervention elements in each country, and differences between the country sites, we will compare the process evaluation variables/ indicators regarding ways in which program services and goods are provided (i.e. deviations) using the t-test statistic or the equivalent non-parametric test. For categorical context variables we will use the chi-square test statistic.
6. To compare changes in participant perceptions towards diabetes, physical activity, dietary behavior; and changes within contexts, as a result of implementing the intervention elements; we use multivariable linear regression mixed effects modeling with a random intercept, unstructured correlation matrix and robust standard errors, to evaluate changes over time in these outcomes of interest in relation to the assigned study arm. Visit month (categorical) at which the outcome is measured, study arm would be included in the model as fixed effects. The null hypothesis to be tested in this analysis would be that the mean changes at all the post-baseline visit months are equal between the treatment groups. The alternative hypothesis would be that the mean changes are not equal at, at least one post-baseline visit month.

We recognize that since sample size calculations for this trial were not based on the secondary outcomes, lack of significant differences in analysis of secondary outcomes might either be true lack of differences in these outcomes, or due to the fact that the trial was not sufficiently powered to detect differences in these outcomes. Thus interpretation of findings on secondary outcomes will be done with caution in case we do not detect any differences.

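### The HbA1c change model names no clustering level, its random intercept cancels from the change contrast, and its robust errors have too few facilities, so type I error exceeds 5% on the natural readings

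*Protocol*

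**What the plan says.** Section 3.1 makes the facility the unit of randomisation: "The health facility clusters will be randomized to either the facility alone arm, or the facility + community arm". Section 3.10 gives the numbers: "Uganda will be working in 9 clusters, Sweden in 4 clusters, whereas South Africa will be working in 2 clusters".

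Table 15 (section 3.8) marks the row "HbA1c (All sites") at baseline and month 12 only.

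Section 3.13.1 opens by proposing GEE to deal with correlation within clusters. It then specifies "mixed effects modeling with a random intercept, unstructured correlation matrix and robust standard errors, to evaluate changes over time in HbA1c". Later it lists GEE again as an option and leaves the choice to the nature of the data. No level is attached to the intercept, the matrix or the robust errors. No facility-by-visit term and no small-sample correction is named.

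Section 3.13.2 item 6 reuses the structure for perceptions, physical activity and diet: "mixed effects modeling with a random intercept, unstructured correlation matrix and robust standard errors, to evaluate changes over time in these outcomes of interest". Its named fixed effects are visit month and study arm.

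**The concern.** In a cluster-randomised trial the standard error of the arm effect must include variation between clusters in the quantity compared. Here that quantity is change in HbA1c over a year, and facilities can differ in it through staffing, drug supply or assay. The only random effect named is an intercept, which absorbs stable differences in level and not differences in change. If nothing else in the analysis carries the facility component, participants are treated as independent replicates of a facility-level allocation. P-values and intervals for the pre-diabetes primary outcome, and for the item 6 outcomes, would then be too optimistic.

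**Working it through.** **Inputs.** Facilities per arm, assuming an equal split: Uganda 9/3 = 3, Sweden 4/2 = 2, South Africa 2/2 = 1; pooled facility + community v facility only, 3 + 2 + 1 = 6 per arm. Planning ICCs for pre-diabetes (section 3.10, Table 16(a)): 0.200 Uganda, 0.044 South Africa, 0.070 Sweden (0.06 in the text).

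**The plan's own figures.** The clustering step is n·k·(1−ρ)/(k−n·ρ) with n = 34:
- Uganda: 34×9×0.8/(9−6.8) = 111.3, so 112, as stated.
- South Africa: 34×2×0.956/(2−1.496) = 129.0, so 129, as stated.
- Sweden: 34×4×0.93/(4−2.38) = 78.1, so 79 with ρ = 0.070; 0.06 gives 66.

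The 34 itself does not reproduce. The text has "in mean HbA1c by month 12 of at least 3 mmol/mol (effect size") and "with a standard deviation of 2.5 mmol/mol in the intervention arm", yet states "at an 80% power and 5% level of significance is 34 participants per arm"; those inputs give 11. That is a separate matter. The cluster sizes below follow from the plan's stated totals: 112/3 = 37.3, 79/2 = 39.5 and 129.

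**What the intercept does.** Write HbA1c for participant i in facility j at visit t as fixed effects + u_j + p_ij + g_jt + e_ijt, where u and p are facility and participant intercepts and g is facility-by-visit variation. Month 12 minus baseline is fixed effects + (g_j,12 − g_j,0) + (e_ij,12 − e_ij,0). Both intercepts are gone. Only g carries facility differences in change, and the plan names no such term.

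**What the unstructured matrix can do.** Two visits give three moments (two variances, one covariance). An unstructured 2×2 matrix uses all three, so a participant intercept on top is a fourth parameter that cannot be identified. Across a whole facility, 41 enrolled participants (124/3) have 82 readings and 82×81/2 = 3,321 correlations; 142 participants have 284 readings and 284×283/2 = 40,186. The matrix is workable only within a participant.

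**Reading A: model-based or participant-level robust errors.** With change ICC ρ and m per facility, the variance is understated by D = 1 + (m−1)ρ, and type I error is 2[1 − Φ(1.96/√D)].

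| Setting | ρ of change | D | Type I error |
|---|---|---|---|
| Uganda 3 v 3, m = 37.3 | 0.01 | 1.36 | 9% |
| | 0.05 | 2.82 | 24% |
| | 0.10 | 4.63 | 36% |
| | 0.20 | 8.27 | 50% |
| Sweden 2 v 2, m = 39.5 | 0.07 | 3.70 | 31% |
| South Africa 1 v 1, m = 129 | 0.044 | 6.63 | 45% |

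Models fitted to simulated null data for Uganda at ρ = 0.20 agree: participant-level GEE rejected 53% (400 runs), and a mixed model with facility and participant intercepts and model-based errors rejected 60% (60 runs only, so imprecise).

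**Reading B: robust errors by facility.** Facility variation in change now enters. With g equal-sized facilities per arm, the uncorrected sandwich variance is (g−1)/g times the unbiased one. The test therefore rejects when |t| on 2g−2 degrees of freedom exceeds 1.96·√((g−1)/g):
- 2 v 2: cut-off 1.386 on 2 df, 30%.
- 3 v 3: cut-off 1.600 on 4 df, 18.5%.
- 6 v 6: cut-off 1.789 on 10 df, 10.4%.
- 1 v 1: no within-arm facility variation to estimate, so no valid test.

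The usual G/(G−1) factor lowers these only to 25%, 15% and 9%. Simulated rates are flat across ρ from 0 to 0.20 (for 3 v 3, 17.5% to 19%), so here the cause is few facilities. A fitted facility-level GEE for Uganda rejected 18% (400 runs). Pooling with the real imbalance in facility size and with site effects gave roughly 20%.

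**Comparison.** A t test on facility mean changes, with df = facilities − 2, rejected 4.5% to 5.5% for 2 v 2, 3 v 3 and 6 v 6.

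**The case against.** The strongest reply is that the text does not exclude facility differences from the standard error. Section 3.13.1 promises robust errors without naming their level, straight after saying that correlation within clusters is to be handled. A within-participant working matrix can be combined with a sandwich grouped by facility. This stands. A reader might infer that facility variation never reaches the standard error, or that the trouble has nothing to do with the number of facilities; the documents support neither. Under Reading B the variation is carried, and the excess error is exactly a few-clusters problem that more facilities would cure.

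Second, Table 16(a) describes the outcome as a mean change. If change is the response and the intercept is the facility's, the intercept is the right facility component. This is a possible reading. But with one change value per participant an unstructured matrix across visits has nothing to act on, so the sentence does not fit that reading well. It would still need small-sample degrees of freedom.

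Third, the sizes in Reading A depend on an ICC of change that the documents do not give separately. The 0.200 was picked from a range of trial values because it gave the largest sample, so it is not an estimate. That is why a range is shown.

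Fourth, such details might be left to a statistical analysis plan. Silence alone would not be a finding. But the protocol specifies a structure, and that structure does not suit its own contrast.

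**Conclusion.** The point holds in this form. As written, the model's random intercept does not protect the change contrast, and the level of every clustering device is unnamed. Under participant-level or model-based errors, type I error is about 9% to 50% for Uganda over change ICCs of 0.01 to 0.20. Under facility-level robust errors without correction it is about 18% for Uganda, 30% for Sweden and 10% or more pooled, with no valid test for South Africa alone.

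Assumptions: facilities split equally between arms; equal facility sizes, except where imbalance is noted; Sweden's four health centres as its clusters (section 3.6.3 describes allocating postal-code zones, which would change the Swedish count); the undoubled 79 per arm for Sweden (doubling it raises the Reading A rate); and the planning ICC applied to change at the top of the range. The facility-level rates do not depend on the ICC. This concerns a primary outcome's error rate, so it should be settled before analysis.

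**What to change.** In section 3.13.1, and identically in section 3.13.2 item 6:

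1. Name the health facility as the clustering level.
2. Either model month-12 HbA1c adjusted for baseline (or change) with a facility random effect, or keep the longitudinal form with an arm-by-visit term and a facility-by-visit random effect.
3. Confine the unstructured matrix to the visits within a participant.
4. Use small-sample inference: REML with Kenward-Roger degrees of freedom, or a t test on facility means with degrees of freedom counted from facilities.
5. State that South Africa alone, at one facility per arm, supports no site-specific test of the arms and contributes only to the pooled analysis.

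The cost is analysis wording only; no data collection changes. The downside is wider intervals, most of all for Sweden alone, where a 2 v 2 comparison leaves 2 degrees of freedom.
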